### Statistical analyses and power

The primary outcomes are changes in child outcomes that will be analysed in multilevel models where a specific intervention-control comparison will be included. Subsequently, we will compare 45 intervention and 45 control centres for environmental quality in order to estimate the effect upon staff behaviour in the centres.

Analyses will be carried out using two different types of dataset:
*The intention-to-treat datasets:* data will be analysed based on participants according to the random allocation, irrespective of whether the intervention was or was not entirely or partly taken up
*The per-protocol datasets*: because it is possible that participants may not receive the intervention, the intention-to-treat analysis might underestimate the potential efficacy of intervention. A per-protocol analysis will, therefore, be carried out in addition to the intention-to-treat analysis. The per-protocol datasets will include data pertaining to all outcomes, restricted to participants who complied fully or partly with their assigned intervention.

Primary analyses will use the intention-to-treat dataset. Centre and participant characteristics at trial entry will also be tabulated using the intention-to-treat datasets.

The effect of the PD intervention will be considered in two ways. Firstly, we will compare 45 intervention and 45 control centres for environmental quality in order to estimate the effect upon staff behaviour in the centres. ECEC room-level outcomes will be analysed using linear regression models with post-test outcomes as dependent variables and baseline measures as independent variables. Child-level data analyses will control for clustering within centres using multilevel models (hierarchical models or random-effect models), which can account for clustering of repeated assessments within individuals and clustering of individuals within centres. Post-test scores for primary and secondary outcomes will be used as dependent variables, with baselines variables and group membership as independent variables. Multiple imputation methods will be used for missing individual outcome data. If data are normally distributed we will fit linear models. If not, we will categorise outcome data and use longitudinal logistic regression to evaluate the differences between intervention and control groups. Sensitivity analyses will be conducted for all primary and secondary outcomes. Inverse probability weighting will be considered if missing data are more prevalent than expected and/or there is differential attrition between trial arms. Additionally, reasons for the differential attrition will be fully explored. Secondary analyses from explicit hypotheses (e.g. subgroup, including level of deprivation) will be specified in advance in a statistical analysis plan.

In applying power calculations, we took into account that children are clustered in centres.

Conservative power estimates, after adjusting for the clustered (nested) design, indicate that we can detect an effect size as low as 0.17 standard deviation (SD) units with 80% power for all child outcomes. This is based on a conservative estimate of 13 children per centre, yielding an estimated sample size of 1170. For continuous outcomes, these correspond to differences between the means in the treatment and control groups in units of the SD.

Detectable effect sizes depend on:The type I error rateThe unit of comparison, i.e. children (*N* = 1170) or centre (*N* = 90)For children, whether measures are independent observations or clustered within centresWhere children are assumed to be clustered within centres, how much of the variability is between centres and how much of the variability is between children within centres

For 80% power, this study would be capable of detecting an effect size for the child outcomes of between 0.17 and 0.20 (*p* < .05) or between 0.21 and 0.24 (*p* < .01), depending on the ratio of the SD of children within centres to the SD of centres. This compares with detectable effect sizes of between 0.16 (*p* < .05) and 0.20 (*p* < .01) if the child measures could be assumed to be independent.

Some of the secondary outcomes involve differences between intervention and control groups at the centre level. Contrasting the child-level outcomes, the differences at the ECEC room level would need to be 0.60 SD units for statistical significance. The design is thus less sensitive for detecting room-level differences than for detecting difference at the child level. While sensitivity for detecting room-level differences could be improved by increasing the sample of centres, the cost implications made this impractical.

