## Methods/design

### Study design

The study employs a clustered randomised controlled trial design. Ninety ECEC centres in NSW, Australia, will be recruited to ensure representation across National Quality Standards (NQS) ratings (Working Towards, Meeting, Exceeding), location (metro, regional), centre type (long-day care and preschool) and socioeconomic areas (as based on the Socio-Economic Indexes for Australia; SEIFA). The sample will ensure representation across these variables, but is not intended to be fully representative of the population (see ‘Centre characteristics and recruitment’ section below). Stratified random assignment of centres to control and intervention groups will occur after the collection of baseline environmental ratings. Once collected, participating centres will then be stratified by centre type and NQS rating and randomly allocated to one of two groups: (1) the *intervention* group (*n* = 45 centres) receiving the PD intervention or (2) the *control* group (*n* = 45 centres) that will continue engaging in typical classroom practice. Fieldworkers, blinded to group allocation, will then conduct baseline child assessments early in the following year. The 9-month PD intervention will occur throughout much of 2016. Post-intervention child assessments and environmental quality ratings will occur again in late-2016 to evaluate any changes as a result of the intervention, relative to control. A flowchart depicting the sequence of recruitment, intervention and assessment for FEEL is shown in Fig. 1. An outline of Standard Protocol Items: Recommendations for Interventional Trials (SPIRIT) time points and actions for the FEEL study is shown in Table 1 (see Additional file 1 for the trial’s SPIRIT Checklist).

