### Randomised allocation of centres

The study will adopt a cluster randomised controlled trial design; participants (i.e. centres and children) will be assigned to the control or intervention groups randomly by cluster (centre). Randomisation will not occur until after: (1) recruitment of centres is complete and (2) initial baseline environment ratings are complete. As such, those involved in recruitment of centres will be unaware, at time of recruitment, to which group centres will be allocated. Stratified randomisation of centres (cluster) will be conducted using centre type and NQS rating as core stratification variables. This randomisation will also be evaluated to ensure comparable socioeconomic status (SES), environmental rating and location profiles between the two groups, which subsequent analyses will confirm.

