#### Phase 3: Model for sustainability (week 3 to month 9)

To promote centre commitment, limit the effects of staff turnover and increase the likelihood of a positive impact, PD support will be provided for the full 9-month intervention through online modules (beginning at the end of phase 1 and continuing for 9 months). Activities and resources, designed to promote staff engagement and establish an online community of educators are contained within modules or *E-books*. Each E-book combines video-streamed content with questions and text, including links to activities and a discussion forum. Staff participation and discussions feed into a learning portfolio, tracking and reflecting how their ideas about pedagogy, children, families and communities have changed. Access to this online environment is provided to all centre staff, not only those attending phases 1 and 2.

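### The supplementary per-protocol analysis drops complete non-takers almost only from the intervention arm; a centre-level complier average causal effect would answer the efficacy question with all randomised centres kept

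*Protocol article*

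**What the plan says.** All of this is in the protocol article.

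- **Primary set** (Statistical analyses and power): "Primary analyses will use the intention-to-treat dataset".
- **Reason for a second set** (same section): "because it is possible that participants may not receive the intervention, the intention-to-treat analysis might underestimate the potential efficacy of intervention". The response is: "A per-protocol analysis will, therefore, be carried out in addition to the intention-to-treat analysis".
- **Rule for that set** (same section): it covers all outcomes but is "restricted to participants who complied fully or partly with their assigned intervention". Only participants with no compliance at all are removed.
- **Control condition** (Study design): control centres are a group "that will continue engaging in typical classroom practice".
- **Unit** (Randomised allocation of centres): "participants (i.e. centres and children) will be assigned to the control or intervention groups randomly by cluster (centre".
- **Online component** (Phase 3): "Access to this online environment is provided to all centre staff, not only those attending phases 1 and 2".

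No compliance rate is given. Inverse probability weighting is mentioned only for missing data and differential attrition, not for selective uptake.

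**The concern.** A control centre has nothing to decline, so the restriction in practice removes intervention centres that took up none of the programme. The remaining intervention centres are then compared with all control centres, including those that would also have taken up nothing if offered it.

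Uptake in Phases 1 and 2 means releasing staff to a hub for two full days and five half-days. That plausibly depends on staffing and leadership, and the Background section itself treats staff quality as a main driver of child outcomes. If non-taking centres differ in this way, the per-protocol contrast mixes the effect of the programme with a difference between kinds of centre. At stake is the one analysis offered to show the efficacy that ITT may understate.

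**Working it through.** **The plan's own figures.** None is given for compliance. The power figures are needed because they imply how much centres can differ. With 1170 children, 13 per centre, the detectable effect at 80% power and two-sided 5% is 2.802 × √(4 × DE / 1170), where DE = 1 + 12 × ICC.

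- Independent children (DE = 1): 2.802 × √(4/1170) = 0.164, matching the stated 0.16.
- Stated 0.17: ICC = ((0.17/2.802)² × 292.5 − 1)/12 ≈ 0.006.
- Stated 0.20: ICC = ((0.20/2.802)² × 292.5 − 1)/12 ≈ 0.041.

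**Bias formula.** Suppose the programme has no effect. Let a share s of intervention centres be excluded and let them score g SD lower for other reasons. With a the mean of the retained centres relative to controls, randomisation gives 0 = (1 − s)a + s(a − g), so a = s × g. This is what the per-protocol comparison would report before baseline adjustment.

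**Assumed inputs.** s = 10 or 20%; g = 0.1 to 0.3 SD. Neither comes from the article. The formula was checked by simulating 45 + 45 centres of 13 children, with ICC 0.04 and the gap added on top, analysing unadjusted centre means over 3000 runs with no true effect.

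| s | g | s × g | Simulated per-protocol estimate | Per-protocol false positives |
|---|---|---|---|---|
| 10% | 0.1 | 0.01 | 0.009 | 5.2% |
| 10% | 0.2 | 0.02 | 0.021 | 5.5% |
| 10% | 0.3 | 0.03 | 0.029 | 6.3% |
| 20% | 0.1 | 0.02 | 0.023 | 6.2% |
| 20% | 0.2 | 0.04 | 0.039 | 8.0% |
| 20% | 0.3 | 0.06 | 0.059 | 11.7% |

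The ITT test stayed at 4.5 to 5.1% throughout. The largest bias, 0.06, is 0.06/0.17 = 35% of the smallest detectable effect.

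**Is the range compatible with the power figures?** A gap g between a share s of centres and the rest creates between-centre variance s(1 − s)g².

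- s = 0.2, g = 0.3: 0.2 × 0.8 × 0.09 = 0.0144. This fits within 0.041 (about 35% of it) but exceeds 0.006.
- At ICC 0.0064 and s = 0.2, g can be at most √(0.0064/0.16) = 0.2, a bias of 0.04.

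**Baseline adjustment.** The plan enters baseline scores as covariates. If the gap is stable over time and the baseline slope is 0.6 to 0.8 (assumed), 0.06 falls to 0.06 × 0.4 = 0.024 or 0.06 × 0.2 = 0.012.

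**The alternative.** When controls have no access to the programme, the complier average causal effect is the ITT difference divided by the uptake share c = 1 − s. With an assumed true complier effect of 0.20 SD, c = 0.8 and g = 0.3, the simulated means were ITT 0.162, per-protocol 0.261 and complier average 0.201. With g = 0, the last two agreed (both 0.202).

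**The case against.** The case for leaving the plan alone has several parts.

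- **Only supplementary.** This stands. A reader might infer that the trial's conclusion is at risk. It is not, because ITT is primary and a per-protocol set beside it is conventional. The compliance threshold may properly be left to the analysis plan, but the exclusion rule and its purpose are already fixed here.
- **Exclusion is not strictly one-sided.** This stands in part. A reader might infer that controls cannot depart from their condition at all. The Abstract describes the comparator as no extra PD, so a control centre that sought other PD might be judged non-compliant. The exclusion is therefore almost entirely, not by construction, from the intervention arm.
- **Few centres would be dropped.** This stands as a limit on size. Partial compliers are kept, centres are volunteers, hubs are within 1.5 h and staff have online access. Complete non-uptake may be rare.
- **Larger biases are not supported.** One could take s = 30% and g = 0.5 SD and infer a bias of 0.15 SD. That needs between-centre variance of 0.3 × 0.7 × 0.25 = 0.0525, more than the whole of the roughly 0.041 implied by the stated power.
- **The unit.** A reader might infer that the rule concerns children and cannot apply to centres. The article's definition of participants includes centres, so it can.
- **The alternative has assumptions too.** This stands. It is not free of bias under every uptake measure. If uptake meant only attendance at Phases 1 and 2, staff who skipped those sessions could still use the online modules. Allocation would then act by a path outside the measure, and the estimate would tend to be inflated.

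**Conclusion.** The concern holds as a modest, cheaply corrected weakness of a supplementary analysis. The per-protocol estimate is not protected by randomisation, and nothing planned addresses selective uptake beyond baseline adjustment. Before that adjustment the bias is about 0.01 to 0.06 SD for assumed s of 10 to 20% and g of 0.1 to 0.3 SD. The top of that range requires an ICC towards the upper end of what the power figures imply.

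After adjustment it is smaller, and only differential growth between centres would escape it entirely. It probably favours the programme, but it would reverse if weaker centres engaged more, and it is zero if non-uptake is unrelated to outcome. The article supplies no compliance rate, so none of these sizes is a prediction.

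**What to change.** For the efficacy question, specify a complier average causal effect at centre level:

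- Use allocation as the instrument for uptake.
- Define uptake as any participation by the centre in Phases 1 to 3, including the online modules. This agrees with the plan's acceptance of partial compliance and closes the online path described above.
- Keep all 90 centres, with the same baseline and stratification covariates as the ITT model and cluster-robust standard errors.
- State the exclusion restriction (allocation affects outcomes only through uptake) and the assumption that controls have no access to the programme.
- If a per-protocol table is kept, label it descriptive.

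**Cost.** One additional model and centre-level uptake records. Phase 3 participation already feeds a learning portfolio; attendance logs for Phases 1 and 2 are presumed, not stated. The interval is wider than the per-protocol one and roughly 1/c times the ITT interval (1/0.8 = 1.25 at 80% uptake). The analysis adds no power over the ITT test and relies on the exclusion restriction. Trial status places post-test assessments from November 2016, so on that schedule the definition can be fixed before outcomes are seen.

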### Outcome measures and procedures

All measures will be administered at baseline and again after the 9-month intervention period (post-test). The battery of child measures was selected to include outcomes that are important for school readiness (i.e. literacy, numeracy, self-regulation, social development). Such outcomes have also been established by previous research as having a foundational role in child development. In total, the child outcome measurements involve 40–50 min of direct assessment per child (split into two sessions) and 10 min of educator time per child (i.e. approximately 3.3 h of educator time per centre) at each data collection time point. In all cases, child assessments will be carried out by a trained fieldworker in a quiet area of the child’s ECEC centre. All environmental quality ratings will also be conducted by highly trained observers through a 1-day observation of each preschool room in participating centres. All observers will need to achieve a rigorous standard of inter-rater reliability with a highly experienced trainer/observer, as indexed by: an intra-class correlation in ratings > .70; a mean difference in ratings < .75; and at least 80% of item ratings within 1 point. In all cases, the researchers involved in collecting baseline and outcome data will be blinded to each centre’s group allocation.

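### The unit of analysis for ECERS-E and SSTEW shifts between room and centre, and the stated room-level regression makes no allowance for rooms sharing a randomised centre

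*Protocol article*

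**What the plan says.** All statements are in the protocol article.

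- **Randomisation** (Randomised allocation of centres): participants "will be assigned to the control or intervention groups randomly by cluster (centre").
- **Measurement** (Outcome measures and procedures): quality ratings are made "through a 1-day observation of each preschool room in participating centres". No rule limits this to one room per centre, and no room count is given.
- **Model** (Statistical analyses and power): "ECEC room-level outcomes will be analysed using linear regression models with post-test outcomes as dependent variables and baseline measures as independent variables".
- **Clustering** (same section, next sentence): "Child-level data analyses will control for clustering within centres using multilevel models". No such allowance is stated for rooms.
- **Comparison** (same section, stated twice): "we will compare 45 intervention and 45 control centres for environmental quality".
- **Power** (same section): the only units listed are children (N = 1170) and centres (N = 90). The text says "Some of the secondary outcomes involve differences between intervention and control groups at the centre level", and then that "the differences at the ECEC room level would need to be 0.60 SD units for statistical significance".

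The labels differ elsewhere too. The Abstract and the outcome descriptions call the two scales room-level. Table 1 lists them as centre-level assessments. Aims of the study calls them centre-level outcomes, and its hypothesis then calls them room-level ratings.

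**The concern.** Rooms in one centre share its management, its allocation and, in the intervention arm, the same online PD modules, which are open to all centre staff. Their ratings are likely to be positively correlated. If two rooms from one centre enter an ordinary regression as separate records, the model treats them as independent evidence about an intervention that was assigned only once. The standard error of the group difference is then too small and the test rejects too often.

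This matters because Aims of the study intends to read effects on child outcomes together with effects on room ratings as evidence that changed practice mediates the child benefit. A falsely significant ECERS-E or SSTEW result would support that claim wrongly.

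The wording also leaves the analyst two different analyses to choose from: 90 centre scores, or a larger unstated number of room scores. That choice should not be open once the data are in hand.

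**Working it through.** **Step 1. Which unit lies behind 0.60 SD?**

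Inputs: 45 units per arm (protocol). 80% power and p < .05 are stated for the child outcomes and assumed here to carry over. Two-sided testing is also assumed.

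Detectable effect = (1.960 + 0.842) × √(2/45) = 2.802 × 0.2108 = 0.591 SD. With the noncentral t it is 0.597 SD. Power at 0.60 SD is 81.2% (normal) or 80.4% (t). The protocol's figure is reproduced.

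If rooms had been counted as independent units, the same formula with 45 × m units per arm would give:

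| Rooms per centre (m) | Units per arm | Detectable effect |
|---|---|---|
| 1 | 45 | 0.59 |
| 1.5 | 67.5 | 0.48 |
| 2 | 90 | 0.42 |
| 3 | 135 | 0.34 |

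So the power statement uses one value per centre, although its sentence speaks of the room level.

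**Step 2. What happens if rooms are entered as separate records?**

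Assumed, because the protocol gives neither: mean rooms per centre m, and within-centre correlation ρ of the ratings after baseline adjustment.

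Design effect DE = 1 + (m − 1)ρ. True type I error = 2 × [1 − Φ(1.96/√DE)].

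Example with m = 2 and ρ = 0.5: DE = 1.5, 1.96/√1.5 = 1.600, type I error 11.0%.

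| m | ρ = 0.1 | ρ = 0.3 | ρ = 0.5 | ρ = 0.7 |
|---|---|---|---|---|
| 1 | 5.0% | 5.0% | 5.0% | 5.0% |
| 1.5 | 5.6% | 6.8% | 8.0% | 9.2% |
| 2 | 6.2% | 8.6% | 11.0% | 13.3% |
| 3 | 7.4% | 12.1% | 16.6% | 20.6% |

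**Step 3. Simulation of the stated model.**

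Null trials, 90 centres, ordinary regression of post-test on group and baseline, 4000 runs per setting, ρ from 0.3 to 0.7. Two separate simulations were run.

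| Rooms per centre | Type I error, centre ignored |
|---|---|
| One in every centre | 5.1 to 5.4% |
| 1 to 3, mean 1.3 | 6.6 to 8.5% |
| About half the centres with 1, half with 2 (mean 1.5) | 7.8 to 10.1% |
| 1 to 3, mean 1.6 | 8.5 to 12.1% |
| 2 in every centre | 8.4 to 13.7% |
| 1 to 3, mean 2.0 | 9.6 to 16.0% |
| 3 in every centre | 12.2 to 21.8% |

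Unequal room counts do more harm than the mean suggests, because the size-weighted mean drives the design effect. With half the centres at 1 room and half at 2, it is (1 + 4)/(1 + 2) = 1.67. DE is then 1.20 at ρ = 0.3 and 1.47 at ρ = 0.7, and the formula gives 7.4% and 10.6%, close to the simulated 7.8% and 10.1%.

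**Step 4. Does respecting the centre repair it?**

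Regression on centre means (n = 90) gave 4.5 to 5.5% in every setting in which it was tried. Cluster-robust standard errors by centre gave 4.7 to 5.9%.

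**The case against.** The strongest reply is that the plan already means one score per centre. The sentence just before the regression sentence compares 45 with 45 centres. The power section lists no unit other than children and centres, and says that sensitivity to room-level differences could be improved by adding centres. Table 1 and Aims of the study place the scales at centre level. The 0.60 SD figure fits 90 values and no larger number. On that reading ordinary linear regression is valid, and averaging to the centre, one of the remedies proposed below, is already the intention.

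Much of this stands. A reader might infer from the room-level regression that the environmental-quality p-values will be too small. The document does not support that. It would require some centres to have several rooms, those rooms to be entered separately, and a positive correlation between them, and the protocol states none of the three. The type I error figures are likewise conditional on assumed values.

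What does not stand is that nothing needs changing. Each preschool room is observed, the model is stated for room-level outcomes, clustering is provided for in the adjacent sentence for children only, and no step turns several rooms into one centre score. Nor is this merely detail left to an analysis plan. The model is fixed here, and what the article explicitly defers to the plan is secondary analyses from explicit hypotheses, such as subgroups.

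**Conclusion.** The point holds as an inconsistency with a conditional consequence. Measurement and model are worded for rooms; the comparison and the power figure are worded for centres. Followed literally, the stated model understates standard errors wherever a centre supplies more than one room record and rooms within it are positively correlated.

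Under assumed correlations of 0.3 to 0.7, type I error would be roughly 7 to 10% at about 1.3 to 1.5 rooms per centre and 8 to 16% at 2 rooms. At a correlation of 0.1 the excess is small (5.6% at 1.5 rooms). With one room per centre or centre-averaged scores it stays at 5%.

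Severity is moderate. Only the secondary outcomes ECERS-E and SSTEW are affected; the child-level primary outcomes are to be analysed in multilevel models.

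**What to change.** State that the centre is the unit of inference for ECERS-E and SSTEW, and choose one of two forms before the post-test ratings are analysed:

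- average the room ratings in a centre to one baseline and one post-test score, and regress post-test on group and baseline with n = 90; or
- keep one record per room, regress post-test on group and baseline, and add a centre random intercept or cluster-robust standard errors by centre.

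Use the same term, room or centre, in the aims, Table 1, the model and the power statement, and report the number of rooms per centre.

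The cost is one sentence. Confidence intervals widen relative to a regression that ignores the centre, by a factor √DE: 1.07 to 1.16 at 1.5 rooms and 1.14 to 1.30 at 2 rooms, for correlations of 0.3 to 0.7. Nothing is lost against the planned sensitivity. With 2 rooms per centre and clustering respected, the detectable effect is 2.802 × √(2 × DE/90), which is 0.48 to 0.55 room-level SD, below the stated 0.60. If every centre has one room, the results do not change.

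### Centres are randomised within centre type and NQS rating, but neither analysis model names these factors; if they are left out, standard errors are somewhat too wide, mainly for room-level outcomes

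*Protocol article*

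**What the plan says.** Under Randomised allocation of centres, the protocol article says: "Stratified randomisation of centres (cluster) will be conducted using centre type and NQS rating as core stratification variables". Study design repeats this. The same allocation section adds: "This randomisation will also be evaluated to ensure comparable socioeconomic status (SES), environmental rating and location profiles between the two groups".

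The models stand under Statistical analyses and power. For children: "Child-level data analyses will control for clustering within centres using multilevel models (hierarchical models or random-effect models"), and then "Post-test scores for primary and secondary outcomes will be used as dependent variables, with baselines variables and group membership as independent variables". For rooms: "ECEC room-level outcomes will be analysed using linear regression models with post-test outcomes as dependent variables and baseline measures as independent variables". Centre type and NQS rating appear in neither description. The only content that this section assigns to a statistical analysis plan is the set of secondary analyses, such as subgroups.

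**The concern.** Stratified allocation balances the arms on centre type and NQS rating, so differences between strata contribute almost nothing to the sampling variation of the treatment contrast. A model without the strata still counts those differences as residual variance. In the multilevel child model they sit in the centre random-effect variance, so allowing for clustering does not remove them. If the strata predict the outcome beyond baseline, the reported standard error is larger than the true one, the test runs below its nominal level and some power is lost.

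This matters most for room-level outcomes. NQS rating is itself a quality rating, the outcomes (ECERS-E and SSTEW) are quality ratings, and centres are selected in roughly equal numbers across the three NQS levels. An association is therefore plausible. The article puts the detectable room-level difference at 0.60 SD and says that adding centres was impractical on cost.

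**Working it through.** **Inputs from the article.** 90 centres, 45 per arm; 13 children per centre, N = 1170; 80% power; detectable child effects 0.17 to 0.20 (p < .05) and 0.21 to 0.24 (p < .01), or 0.16 and 0.20 if independent; room-level difference 0.60 SD. Two-sided tests are assumed.

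**Step 1: the article's own figures.** Detectable effect = (z for alpha + z for power) × 2/√N × √(1 + 12 × ICC).
- Independent: 2.8016 × 2/√1170 = 0.164 at 5%, and 0.200 at 1%. Stated: 0.16 and 0.20.
- Clustered: 0.17 implies ICC = [(0.17/0.1638)² − 1]/12 = 0.006, and 0.20 implies 0.041. The 1% figures imply 0.009 to 0.037.
- Room level: 2.8016 × 2/√90 = 0.591, or 0.597 with the t distribution on 88 df. Stated: 0.60.

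All reproduce. None uses the strata, so none is made wrong by this point. The implied ICC is about 0.006 to 0.041.

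**Step 2: child outcomes, no baseline score.** The variance of a centre mean is ICC + (1 − ICC)/13. Let the strata explain a share R² of the ICC part (assumption: 0.3).
- ICC 0.0064: 0.0828 against 0.0828 − 0.0019 = 0.0809. SE ratio 1.012, type I error 0.047.
- ICC 0.041: 0.1148 against 0.1148 − 0.0123 = 0.1025. SE ratio 1.058, type I error 0.038.

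**Step 3: child outcomes with the baseline score, as planned.** 90 centres in six strata were simulated 8000 times per setting, with R² = 0.3 and the strata shifting baseline and post-test equally. The table gives model SE / actual SE, with type I error in brackets.

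| ICC | Baseline correlation | Strata omitted | Strata included |
|---|---|---|---|
| 0.0064 | 0.7 | 0.996 (0.049) | 0.993 (0.049) |
| 0.041 | 0.7 | 0.998 (0.054) | 0.989 (0.056) |
| 0.041 | 0.5 | 1.015 (0.047) | 0.999 (0.050) |
| 0.10 | 0.7 | 1.003 (0.047) | 0.992 (0.051) |

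Simulation error is about 1/√16000 = 0.8% on the ratio and √(0.05 × 0.95/8000) = 0.0024 on the type I error. A closed form agrees. With Vs = R² × ICC, Vw = (1 − R²) × ICC + (1 − ICC)/13, baseline correlation ρ and slope b = (Vs + ρVw)/(Vs + Vw), the SE ratio is √{1 + Vs(1 − b)²/[Vw(1 − 2bρ + b²)]}. At ICC 0.041 and ρ = 0.5, Vs = 0.0123, Vw = 0.1025 and b = 0.554, so the ratio is √1.0318 = 1.016. With ρ = 0.7 it is 1.008, and at ICC 0.0064 with ρ = 0.7 it is 1.002. The excess is therefore about 0 to 1.5%.

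**Step 4: room-level outcomes.** Let the strata explain a share R² of the variance left after the baseline rating (assumption: 0.1 to 0.2). SE ratio = 1/√(1 − R²); true type I error = 2[1 − Φ(1.96/√(1 − R²))].
- R² = 0.1: SE 5.4% too large, type I error 0.039.
- R² = 0.2: SE 11.8% too large, type I error 0.028.

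Detectable difference under stratified allocation, in units of the SD left after baseline:
- Strata omitted: (1.96 + 0.8416 × √(1 − R²)) × 2/√90 = 0.582 and 0.572.
- Strata included: 2.8016 × √(1 − R²) × 2/√90 = 0.560 and 0.528.

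If the strata add nothing after baseline, the ratio is 1 and nothing is lost.

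**The case against.** The strongest reply is that the omission is not established. The child model's baseline variables are plural and undefined, and centre type and NQS rating are known before allocation, so they could be among them. The paragraph is condensed: the room-level sentence does not even name the group term, although that model exists to compare the arms. Covariate lists are also often left to an analysis plan. This stands in part, since nothing says that the strata will be excluded. But the article does state its model terms here and sends only secondary analyses to the analysis plan. It says that all measures are administered at baseline, so the room model's baseline measures most naturally means the baseline ECERS-E and SSTEW ratings.

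Three stronger readings are tempting, and the document does not support them.
- A reader might infer that the check on socioeconomic status, environmental rating and location further restricted the randomisation. Only centre type and NQS rating are named as stratification variables, and no acceptance rule or redraw is described. Without one, omitting the other three does not make the standard error invalid. The baseline environmental rating is in any case already in the room model.
- A reader might infer that the primary test runs well below 5%. That requires ignoring the baseline score, which the stated model contains; with it, the simulated type I error is 0.047 to 0.054.
- A reader might assume an ICC of 0.10, where the calculation without baseline gives an SE 10.2% too large (√(0.1692/0.1392) = 1.102). That ICC lies outside the 0.006 to 0.041 implied by the article, and even there the simulated ratio with baseline is 1.003.

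**Conclusion.** The point holds as a mismatch between design and stated analysis: the trial randomises by two factors that neither model names. Any error is conservative. It brings no bias and no excess of false positives, and the article's power figures stand.

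For the primary child outcomes the effect is negligible to slight, about 0 to 1.5% of the standard error, assuming strata R² of 0.3, baseline correlation of 0.5 to 0.7, equal cluster sizes and strata that act alike on baseline and post-test. For the secondary room-level outcomes it could matter: about 5 to 12% of the standard error, with true type I error of about 0.039 to 0.028, if the strata explain 10 to 20% of the variance remaining after baseline. The article gives no figure for that share. It does not support a claim that the intervals are wrong as a matter of fact.

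**What to change.** Under Statistical analyses and power, state that both the child model and the room model include fixed effects for centre type (two levels) and NQS rating (three levels), alongside the baseline score and group. As main effects these use 1 + 2 = 3 of about 88 centre-level degrees of freedom. Both factors are known for every centre before allocation, so no data collection is needed. The sentence also settles what the child model's baseline variables are.

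Adjustment for SEIFA, location and, in the child model, environmental rating is optional. The exception is if the balance check led to any allocation being rejected. Those variables should then also be adjusted for, and the acceptance rule reported.
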